### 2.7. Reference Standard for Sarcopenia

The presence and the stage of sarcopenia will be determined following the recommendations provided by the European Working Group on Sarcopenia in Older People 2 (EWGSOP2) [2]. Accordingly, muscle strength will be determined through repeating sit-to-stand test five times, with a cut-off point higher than 15 s representing probable sarcopenia. Then, sarcopenia will be confirmed by appendicular skeletal muscle mass with a cut-off point lower than 20 and 15 kg for men and women, respectively. Appendicular skeletal muscle mass will be determined using bioelectrical impedance analysis (TANITA MC-580, Tanita Corp., Tokyo, Japan). Resistance index and reactance values will be used in the validated equation developed by Sergi et al. [22] as recommended by the EWGSOP2 [2]. Low physical performance will be assessed using the Short Physical Performance Battery test (SPPB) [23]. A score lower than 9 points will be indicative of low function and, therefore, severe sarcopenia. The EWGSOP2 recommends this tool for assessing the degree of severity of sarcopenia [2].

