## Abstract

Prefrailty and sarcopenia in combination are more predictive of mortality than either condition alone. Early detection of these syndromes determines the prognosis of health-related adverse events since both conditions can be reversed through appropriate interventions. Nowadays, there is a lack of cheap, portable, rapid, and easy-to-use tools for detecting prefrailty and sarcopenia in combination. The aim of this study is to validate an iPhone App to detect prefrailty and sarcopenia syndromes in community-dwelling older adults. A diagnostic test accuracy study will include at least 400 participants aged 60 or over without cognitive impairment and physical disability recruited from elderly social centers of Murcia (Spain). Sit-to-stand muscle power measured through a slow-motion video analysis mobile application will be considered as the index test in combination with muscle mass (calf circumference or upper mid-arm circumference). Frailty syndrome (Fried’s Phenotype) and sarcopenia (EWGSOP2) will both be considered as reference standards. Sensibility, specificity, positive and negative predictive values and likelihood ratios will be calculated as well as the area under the curve of the receiver operating characteristic. This mobile application will add the benefit for screening large populations in short time periods within a field-based setting, where space and technology are often constrained (NCT05148351).

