### 2.5. Index Test: Smartphone Mobile Application (App)

Participants’ sit-to-stand capacity will be assessed using an iPhone App called *Sit-to-Stand* (version 1.1.1.) installed on an iPhone 13 device running iOS 15.3; Apple Inc., Cupertino, CA, USA. This App was created to determine muscle power derived from one time rise from a chair using a slow-motion video captured camera (240 frames per second). Participants will sit on a rigid and adjustable height chair with their arms crossed over their chest with their hip, knee and ankle joints visually positioned at 90 degrees. Then, subjects will be instructed to stand from the chair “as fast as possible”, while the execution of the test will be filmed simultaneously with the smartphone. The smartphone will be placed horizontally on a 0.7 m-high tripod placed 3 m from the right or left side of the participant. This App estimates muscle power relative to body weight (in watts per kilogram; W/kg) from the subsequent analysis of the video recording using the following equation:*Muscle Power* = 2.773 − 6.228 × *t* + 18.224 × *d*
where *t* is the time to rising, i.e., the time from seat off until the hip and knee joints reach full extension in an upright stance, and *d* is the femur length of the subject, i.e., the vertical displacement during the sit-to-stand test. Femur length will be measured as the distance between the superior aspect of the greater trochanter and femoral lateral condyle on the participants’ right or left side. A reflective marker will be placed on the greater trochanter in order to identify the start and end of the sit-to-stand movement. The start of the movement is determined when the pelvis began to move forward after anterior trunk tilt which is time-matched when the reflective marker crossed the first horizontal grid line on the screen of the App (Figure 1). The end of the movement is defined when full extension of hip and knee is achieved in an upright stance which is time-matched when the reflective marker achieves the highest vertical point during the upright movement cycle. The results provided from this App has been twice validated against 3D motion capture camera and force plates in community-dwelling older adults [14,15].

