### 2.6. Reference Standard for Frailty Syndrome

Frailty syndrome will be assessed through frailty phenotype proposed by Linda Fried [20]. Although there is no gold standard for the detection of frailty, this tool is probably the most used in the scientific literature [3]. This multidimensional tool determines frailty through five domains: gait speed, exhaustion, unintentional weight loss, strength and physical activity levels. Gait speed will be assessed using the 4 m gait test at usual and comfortable pace. Unintentional weight loss will be assessed by asking the subject if he/she experienced unintentional weight loss over 4.5 kg through the previous year. Exhaustion assessment will be collected asking to participants to rate from 0 (never) to 3 (most of the time) the frequency with which they experience the following statements: “I felt that everything I did was an effort” and “I could not get going”. Strength level will be assessed using handgrip strength with a Takei 5401 hand grip digital dynamometer (Takei Scientific Instruments Co., Ltd., Tokyo, Japan) and data relative to the physical activity levels of the participants will be collected through the Spanish validated short version of the Minnesota leisure time physical activity questionnaire [21]. The presence of at least 3 of 5 criteria will be necessary to define a frail state, whereas the presence of at least 1 criterion will be sufficient to identify prefrailty state [20].

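### The sarcopenia reference and the index test share the chair-rise task, so accuracy is likely optimistic; prespecify a grip-based second reference alongside it

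*Protocol article*

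**What the plan says.** - **Index test.** The Abstract states: "Sit-to-stand muscle power measured through a slow-motion video analysis mobile application will be considered as the index test", in combination with calf or mid-upper-arm circumference. Section 2.5 adds: "This App was created to determine muscle power derived from one time rise from a chair". Power is 2.773 − 6.228 × t + 18.224 × d, where d is femur length and t is "the time from seat off until the hip and knee joints reach full extension in an upright stance".
- **Sarcopenia reference, strength step.** In section 2.7, "muscle strength will be determined through repeating sit-to-stand test five times", "with a cut-off point higher than 15 s representing probable sarcopenia". No other strength measure is named for sarcopenia.
- **Sarcopenia reference, confirmation.** Section 2.7 continues: "sarcopenia will be confirmed by appendicular skeletal muscle mass with a cut-off point lower than 20 and 15 kg" for men and women respectively, by bioimpedance.
- **Grip.** Section 2.6: "Strength level will be assessed using handgrip strength with a Takei 5401 hand grip digital dynamometer". It serves only the frailty phenotype. The five frailty domains listed there include no chair stand.
- **Timing.** Section 2.4 puts all measurements on one day, with the index test before the frailty and sarcopenia assessments.
- **Analysis.** Section 2.9 estimates AUC and cut-offs for power against each syndrome and both combined, then for a logistic model of power plus a circumference. Sensitivity, specificity, predictive values and likelihood ratios follow.
- **Limitations.** Section 3 names the retrospective design and the probably fitter attendees of social centers. It does not mention that index and reference share a task.

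**The concern.** For a given femur length, rise time alone sets the app score: a rise 0.1 s slower lowers it by 0.1 × 6.228 = 0.62 W/kg. The gate to a sarcopenia diagnosis is also a chair-rise time. As section 2.7 is written, someone who finishes five rises within 15 s cannot be a sarcopenia case or a combined case, whatever their muscle mass or grip.

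Influences specific to rising from a chair (technique, a painful knee, effort that day) therefore push the index and the reference the same way, whether or not they reflect sarcopenia. The accuracy figures then measure in part the agreement between two chair-rise tests. The Introduction argues for instrumented power partly because it discriminates frailty better than the time to complete the test. For sarcopenia, that completion time is one of the two components of the reference. A reader of the results could not see how much of the accuracy comes from the shared task.

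**Working it through.** **The plan's own figure.** The only computed figure is 200 participants per sex (section 2.8). The overlap does not change it, and the null value it rests on is not stated, so it is not the test here. The documents give no correlation among power, five-rise time, grip and muscle mass. What follows is an illustration on assumed values.

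**Side by side.**

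| | Index (2.5) | Sarcopenia strength gate (2.7) | Grip (2.6) |
|---|---|---|---|
| Task | one chair rise, maximal speed | five chair rises | hand dynamometer |
| Result | W/kg from rise time and femur length | total time, more than 15 s | strength |
| Used for | the test under study | sarcopenia and combined target | frailty only |

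The two chair-rise results are separate measurements of one motor task.

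**Model (all values assumed).** Standardised variables, higher meaning better, 400,000 simulated subjects per scenario:
- power = a·S + √s·T + error
- five-rise performance = a·S + √s·T + error
- grip = a·S + error
- muscle mass = 0.4·S + error

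S is general strength. T is shared by the two chair-rise tests and absent from grip. Hence corr(power, five-rise) = a² + s and corr(power, grip) = a². Low strength is the lowest 25%, low mass the lowest 40%, and sarcopenia requires both (prevalence about 12–14%).

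**AUC of power alone for sarcopenia.**

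| a | s | corr. with five-rise | corr. with grip | AUC, five-rise reference | AUC, grip reference | Gap |
|---|---|---|---|---|---|---|
| 0.5 | 0.1 | 0.35 | 0.25 | 0.682 | 0.645 | 0.037 |
| 0.5 | 0.4 | 0.65 | 0.25 | 0.795 | 0.646 | 0.149 |
| 0.6 | 0 | 0.36 | 0.36 | 0.693 | 0.694 | −0.001 |
| 0.6 | 0.1 | 0.46 | 0.36 | 0.730 | 0.694 | 0.036 |
| 0.6 | 0.3 | 0.66 | 0.36 | 0.803 | 0.693 | 0.110 |
| 0.6 | 0.4 | 0.76 | 0.36 | 0.843 | 0.692 | 0.151 |
| 0.7 | 0.1 | 0.59 | 0.49 | 0.781 | 0.745 | 0.036 |
| 0.7 | 0.4 | 0.89 | 0.49 | 0.897 | 0.746 | 0.151 |

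The gap depends almost entirely on s: about 0.04 at s = 0.1, about 0.15 at s = 0.4, and none at s = 0.

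**Adding circumference, as section 2.9 plans.** I added a circumference correlated 0.5 or 0.7 with muscle mass (assumed) to the same model and used the AUC of the fitted logistic regression. For s from 0.1 to 0.4 the gap falls to about 0.02–0.13. The grip-based AUC rises to about 0.71–0.82. A separate set-up with correlations specified directly gives a gap of 0.02–0.14 with circumference. The gap shrinks but does not vanish.

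**What this does not cover.** The target simulated is sarcopenia, not the combination with prefrailty. T is whatever the two chair-rise tests share and grip lacks. It may be a task artefact or genuine leg strength, and the model cannot separate them.

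**The case against.** **The app result is not part of the reference.** This stands. One fast rise timed from video and a total for five rises are different measurements, and bioimpedance muscle mass must confirm the diagnosis. A reader might infer incorporation bias in the strict sense, or that the app predicts a repeat of itself. The documents do not support that, because a slow five-rise time does not fix single-rise power.

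**The five-rise test follows the cited consensus.** This also stands. Section 2.7 presents it so, and the Introduction calls chair-rise time a criterion for probable sarcopenia. The definition is not wrong in itself. The weakness is that it is the only strength criterion used to judge a chair-rise index.

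**The gap is assumed, and grip is a different construct.** This stands in part. A lower AUC against grip does not prove inflation, since grip may share less with leg function. That limits any claim about size. It does not remove the expected upward direction when task-specific variance is shared.

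**Grip should simply replace the five-rise criterion.** This is tempting but not supported. Under section 2.6 one criterion suffices for prefrailty, and low grip is one. If the sarcopenia grip cut-off lies at or below the frailty cut-off, every grip-defined sarcopenia case is prefrail by definition. The combined target then collapses towards sarcopenia, and the sarcopenia-only group in section 2.9 empties. Neither grip cut-off is given in the article.

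**An analysis plan might cover it.** The reference standard is fixed in section 2.7, so this is a stated choice rather than a detail left for later.

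**Conclusion.** The point holds as task overlap with correlated measurement. It concerns sarcopenia and the combined target, not the frailty reference alone. Accuracy is likely optimistic by an amount that the documents cannot give. Under the assumed correlations, the AUC difference between a five-rise and a grip-based reference is roughly 0.04–0.15 for power alone, smaller with circumference, and zero if the two chair-rise tests share nothing that grip lacks. Part of any difference may be real.

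A reader might also infer that the overlap alone decides whether the study reaches an AUC of 0.80. That is not shown. Section 2.8 uses 0.80 as a sample-size input, not as a success criterion, and with circumference added some scenarios exceed 0.80 against both references. Nor is the study unable to examine the question, because five-rise time, grip and muscle mass are all recorded. What is missing is a stated analysis that uses them and an acknowledged limitation. This should be fixed; it does not invalidate the design.

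**What to change.** 1. Keep the five-rise definition in section 2.7 as the primary sarcopenia reference.
2. In sections 2.7 and 2.9, prespecify a second sarcopenia reference in which low strength is defined by the handgrip from section 2.6, with the muscle-mass step unchanged. The sponsor should confirm in reference [2] that grip is admitted and take the cut-offs from there.
3. Report AUC, sensitivity and specificity with confidence intervals against both references side by side, for sarcopenia and for the combined target, for power alone and for power plus circumference.
4. State the shared chair-rise task as a limitation in Section 3, with the expected direction of its effect.

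The cost is protocol wording and some extra analysis, with no new measurement. The second AUC may be less favourable. Grip would enter both the frailty and the sarcopenia definitions in the second analysis, and this should be stated when its combined-target result is interpreted.

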### 2.8. Sample Size Estimation

Since the prevalence of both syndromes (prefrailty and sarcopenia) in combination has been reported in a range from 13% to 40% in Spanish community-dwelling older adults [9,10], sample size was estimated according to the lowest prevalence rate to be more confident. Therefore, a minimum sample size of 200 participants per sex was estimated in accordance with Bujang and Adnan [24] to detect an effect size equal or higher than 0.80 area under the curve (AUC), with an alpha error of 0.05 and statistic power of 80%. Since the study aim is to develop a specific tool to be used as a diagnostic tool, a high degree of both sensitivity and specificity is usually necessary (for a detailed information, see Tables/Figures 1–3 in [24]).

### 2.9. Statistical Analysis

The database will be created in Microsoft Excel©, Microsoft Corp., Redmond, WA, USA and the software IBM SPSS Statistics 26.0, SPSS Inc., Chicago, Ill, USA will be used for further analysis. A descriptive analysis of data will be carried out to report the participants’ characteristics. We will provide values represented as mean, standard deviation, and 95% confidence interval (CI) for continuous variables and frequencies and percentages for categorical variables. Kolmogorov–Smirnov’s test will be used to assess the normal data distribution. A data scrub will be performed with range and logic tests and we will search for unknown or unlikely values.

A complete case analysis will be performed. The AUC of the receiver operating characteristic (ROC) will be calculated to identify the best cut-off point of muscle power to discriminate subjects with both syndromes separately and in combination. Then, a multiple logistic regression equation with muscle power and calf circumference or mid upper-limb circumference will be generated and an additional ROC analysis will be performed using predictive probability from the results of the multiple logistic regression analysis to identify the best cut-off point for detecting both syndromes for each sex. Cross-tabulations of the index test with the reference standards (prefrailty and sarcopenia syndromes) will be performed and sensibility, specificity, positive and negative predictive values, and positive and negative likelihood ratios will be calculated. Finally, after classifying the status of the subjects into robust, prefrail, sarcopenia or the combination of both syndromes, the chi-square tests will be used to assess differences in proportion regarding their clinical profile (Table A1) and the Odds Ratio with 95% CI will be calculated.

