Recent advances in hand-held technology offer an opportunity to assess muscle power during sit-to-stand test through a smartphone mobile application as valid as a force plate and 3D motion capture cameras [14,15] with the advantage of acquiring muscle power with a short assessment duration and automatic data processing response. Indeed, the purpose of this study is to develop and validate an update of the *Sit-to-Stand* App for detecting prefrailty and sarcopenia syndromes in combination in community-dwelling older adults. Since several studies have shown that low muscle mass measured by calf circumference or mid upper-arm circumference has been associated with frailty and sarcopenia syndromes [16,17], one could expect that the incorporation of these two measures, muscle power and muscle mass, into a single diagnostic tool integrated in a mobile application will result in a portable and unique easy-to-use tool capable of early detecting both syndromes in combination with enough accuracy. This mobile application will add the benefit for screening large populations in short time periods within a field-based setting, where space and technology are often constrained.

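### Cut-offs and the logistic equation are derived and scored in the same participants with no optimism correction, so sensitivity will on average be overstated and the study develops the tool rather than validates it

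*Protocol article*

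**What the plan says.** The aim is stated as validation. The Abstract says "The aim of this study is to validate an iPhone App to detect prefrailty and sarcopenia syndromes". The Introduction says "the purpose of this study is to develop and validate an update of the" Sit-to-Stand App, and the Discussion (section 3) repeats this aim.

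Section 2.9 sets out the analysis in order:

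1. An ROC analysis of muscle power is run "to identify the best cut-off point of muscle power to discriminate subjects with both syndromes separately and in combination".
2. Then "a multiple logistic regression equation with muscle power and calf circumference or mid upper-limb circumference will be generated".
3. Next, "an additional ROC analysis will be performed using predictive probability from the results of the multiple logistic regression analysis", and its purpose is "to identify the best cut-off point for detecting both syndromes for each sex".
4. "Cross-tabulations of the index test with the reference standards (prefrailty and sarcopenia syndromes) will be performed", from which sensitivity, specificity, predictive values and likelihood ratios are calculated.

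All four steps use the complete cases of one cohort. The article mentions no holdout set, cross-validation, bootstrap, cut-off fixed in advance or second cohort. In section 2.8, "a minimum sample size of 200 participants per sex was estimated", based on the lowest rate in a reported prevalence range of 13% to 40% for prefrailty and sarcopenia combined.

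**The concern.** A cut-off chosen because it separates these particular participants best will look better in them than in new people from the same population. A regression fitted to the same data adds to this. The accuracy figures from step 4 are therefore apparent accuracy. They describe how a rule was developed and do not test it, although the stated aim includes validation.

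The effect is largest where cases are few. Sensitivity rests only on the cases, while specificity rests on the much larger group of non-cases. If sensitivity is reported too high, users of the App will miss more affected people than the publication leads them to expect. Section 2.8 itself says that a diagnostic tool needs both high sensitivity and high specificity.

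**Working it through.** **The plan's own figure.** Section 2.8 gives 200 per sex for AUC 0.80, alpha 0.05 and power 80%, but no null value and no sidedness, so 200 cannot be rebuilt from the text alone. It is consistent with a one-sample test of sensitivity, n = [(z_α√(p0(1−p0)) + z_β√(p1(1−p1))) / (p1−p0)]², divided by prevalence:

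- 0.70 against 0.90, one-sided: [(1.645×0.458 + 0.842×0.300)/0.20]² ≈ 25.3, so 26 cases; 26/0.13 = 200.
- 0.50 against 0.80, two-sided: [(1.960×0.500 + 0.842×0.400)/0.30]² ≈ 19.3, so 20 cases; 20/0.10 = 200.

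The nulls here, and the 10% prevalence in the second line, are assumptions. The figure of 200 is not shown to be wrong, and nothing below depends on how it was obtained.

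**Cases per sex.** 200 × 0.13 = 26 at the planning prevalence; 200 × 0.40 = 80 at the upper end.

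**Simulation of the section 2.9 sequence.** There were 3,000 runs per setting. The following are assumptions, not taken from the article: best means the maximum Youden index (sensitivity + specificity − 1); markers are normal with equal variance; in the two-predictor equation, 80% of the squared separation comes from power and 20% from circumference; the true AUC of the rule is 0.80. An AUC of 0.80 corresponds to a separation of √2 × Φ⁻¹(0.80) = 1.190 SD. The best possible cut-off then gives sensitivity = specificity = Φ(1.190/2) = 0.724. Each fitted rule was scored in its own sample (apparent) and in new participants (true).

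| Setting | AUC, apparent / true | Sensitivity, apparent / true | Specificity, apparent / true | Excess in sensitivity |
|---|---|---|---|---|
| 200, 13%, power alone | 0.800 / 0.800 | 0.775 / 0.696 | 0.740 / 0.731 | 0.079 |
| 200, 13%, power + circumference | 0.804 / 0.795 | 0.780 / 0.686 | 0.744 / 0.733 | 0.094 |
| 200, 13%, better of two circumferences kept | 0.811 / 0.795 | 0.788 / 0.685 | 0.747 / 0.734 | 0.103 |
| 200, 40%, power alone | 0.800 / 0.800 | 0.746 / 0.710 | 0.743 / 0.724 | 0.036 |
| 200, 40%, power + circumference | 0.802 / 0.798 | 0.749 / 0.709 | 0.745 / 0.723 | 0.040 |
| 400 (sexes pooled), 13%, power alone | 0.799 / 0.800 | 0.761 / 0.712 | 0.729 / 0.722 | 0.049 |

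For the two-predictor equation at 13%, sensitivity plus specificity was overstated by 0.105 on average, and by more than zero in 91% of runs.

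**Range.** Over prevalence 13% to 40% and true AUC 0.70 to 0.90, the two-predictor equation overstated sensitivity by 0.03 to 0.11, specificity by 0.01 to 0.03 and AUC by 0.003 to 0.018. At 40% prevalence alone, the excess in sensitivity was 0.03 to 0.05 over the same AUC values.

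**Second set-up.** With power itself at true AUC 0.80, circumference at 0.60 and the better circumference kept, a separate simulation at 26 cases and 174 non-cases gave sensitivity 0.79 against 0.70 and AUC 0.813 against 0.799, in close agreement.

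**What it means in use.** Taking the means in the second table row, the rule would appear to miss 1 − 0.780 = 22% of cases but would miss 1 − 0.686 = 31%. The negative likelihood ratio would appear as 0.220/0.744 = 0.30 rather than 0.314/0.733 = 0.43. The positive one would appear as 0.780/0.256 = 3.0 rather than 0.686/0.267 = 2.6.

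**The case against.** The strongest reply is that this is a condensed article, that resampling detail often sits in an analysis plan, and that section 3 already says the design limits external validity and that a prospective validation should follow. Part of this stands: the article does not claim that the cut-offs are final, and no section commits to releasing them straight after this study. But section 2.9 spells out a complete sequence which, followed as written, ends in uncorrected accuracy figures. Section 3 links possible shifts in sensitivity and specificity to a fitter sample. Optimism is a different problem: it appears even in new participants from the same centres, and the article neither names nor corrects it.

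Some stronger readings are tempting but go beyond the document:

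- *All accuracy measures, including AUC, are seriously inflated.* They are not. The AUC of power alone needs no cut-off, and the App's power equation is fixed in section 2.5. The equation's AUC moves by 0.02 at most.
- *Confidence intervals will be too narrow.* Section 2.9 gives no interval method for sensitivity, specificity or AUC, so there is nothing to judge.
- *Adding a circumference is bound to look helpful.* A wholly uninformative circumference, fixed in advance, raised the in-sample AUC in about 70% of 2,000 simulated runs, by 0.004 on average. That is not every time, and no test of the gain is planned.
- *Calf or arm will be chosen on the data.* The word *or* leaves this open; reporting both models fits the text equally well.
- *Every analysis is split by sex with 26 cases.* The split is stated only for the logistic step. Pooled power cut-offs would carry less optimism (0.049 in the table), and each syndrome taken separately has at least as many cases as the combination.

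**Conclusion.** The point holds for accuracy measured at a data-chosen cut-off, and for the word *validate*. Followed as written, section 2.9 will on average overstate sensitivity by about 0.08 to 0.10 per sex at 13% prevalence and about 0.03 to 0.05 at 40%. Predictive values and likelihood ratios inherit the error. Specificity is overstated by about 0.01 to 0.03 and the combined equation's AUC by about 0.01 to 0.02; the AUC of power alone is essentially unaffected. Choosing the circumference on the data would make the optimism slightly larger.

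These sizes rest on a Youden cut-off, binormal markers and a true AUC near 0.80, none of which the article states. They are averages, so a single study may show more or less. The direction for sensitivity was the same throughout the range examined. The lower prevalence deserves weight because the sponsor planned on it and section 3 expects a fitter sample than the wider community.

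**What to change.** In section 2.9, add a bootstrap internal validation within each sex (for example 500 to 1,000 resamples) that repeats every data-driven step in each resample: any choice between calf and arm, the logistic fit, and the cut-off search by whatever criterion defines best. If the power cut-off is set for both sexes together, resample at that level for that step.

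Report optimism-corrected sensitivity, specificity, likelihood ratios and AUC as the main results, with the apparent values beside them. State that the correction is incomplete. In a small check (150 replicates of 60 resamples), it brought the Youden index from 0.541 to 0.461 against a true 0.426, which removes (0.541 − 0.461)/(0.541 − 0.426) = 0.080/0.115, or about 70%, of the optimism.

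In the Abstract, Introduction and Discussion, change the aim to developing and internally validating the tool, and leave validation of the locked equation and cut-offs to the later prospective study.

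The cost is some scripting, possibly outside the default SPSS menus, and slightly less favourable reported accuracy. No further participants or measurements are needed.
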